##### ii) Secondary outcomes

##### Adherence to all NRT prescribed, consumed in the first seven days

This will be assessed in the same way as described for the primary outcome described above, but using the time period of the first seven days of the quit attempt.

##### Validated abstinence from smoking at 28 days and six months

At six months, 7-day point prevalence and six month prolonged abstinence will be recorded. Point prevalent abstinence is defined as smoking not more than 5 cigarettes for the seven days prior to the assessment confirmed by salivary cotinine < 15 ng/ml. Prolonged abstinence (defined as sustained abstinence after an initial two week grace period as recommended by Hughes and colleagues [39] will be operationalised by: a) self-reported consumption of not more than five cigarettes since the quit date; and b) salivary cotinine levels of less that 15 ng/ml [40]. A 28-day abstinence measure will also be reported, with validation by carbon monoxide less than 10 ppm, with backward inference of missing data from the 6 month measure following Russell standard criteria [40].

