### Trial medication

The trial will take place in the context of NHS stop smoking services, which provide behavioural support and medication to assist smoking cessation. At the time that this trial started, more than 70% of smokers in these clinics used nicotine replacement therapy (NRT) [28]. Current best practice is to use NRT in combination with behavioural support [31,32]. Smokers in the current trial will all be prescribed NRT patches plus oral NRT 'top-up' medication, which is approximately 35% more effective than NRT patch alone [33]. NRT patch dose will be tailored in the same way in both arms of the trial, namely according to how many cigarettes are smoked per day. Oral NRT dose will be determined on a different basis in each arm of the trial: those in the genotype arm will have the dose tailored according to the *OPRM1 *variant that they carry; those in the phenotype arm will have the dose tailored according to their nicotine dependence. Details of the basis for these prescriptions are presented below. The aim of treatment is to continue with full dose NRT for the first four weeks after the quit day, after which medication is reduced, according to patient need.

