#### Hypothesis II

##### i) Within-subgroup outcome: Motivation to make another quit attempt

The sub-group comprises those participants who fail to achieve prolonged abstinence at the six month follow-up. The primary outcome within this subgroup is motivation to stop smoking in the next four weeks.

This is measured using the mean score of the following four items measured using 7-point bipolar scales: "Do you intend to stop smoking in the next 4 weeks?"[response scale labelled at each end: "definitely do not" (1) and "definitely do" (7)]: "How likely is it that you will stop smoking in the next 4 weeks?" ["very unlikely" (1), and "very likely" (7)]; "How determined are you to stop smoking in the next 4 weeks?" ["not at all" (1), and "extremely" (7)]; and "How much do you want to stop smoking in the next 4 weeks?" ["not at all" (1), to "very much" (7)].

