#### Hypothesis II: within-subgroup outcome

Amongst those classified as not abstinent at the six month follow-up, as judged by 7-day point prevalence abstinence, an independent-samples t-test will be used to compare motivation to make another quit attempt between arms.

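### Six-month abstinence is verified by cotinine alone, with no stated provision for people still using NRT, so some non-smokers can be counted as not abstinent and enter the Hypothesis II subgroup

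*Protocol article*

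**What the plan says.** In the protocol article, *Validated abstinence from smoking at 28 days and six months* defines two six-month measures. Seven-day point prevalence allows up to five cigarettes in the week and must be "confirmed by salivary cotinine < 15 ng/ml". Prolonged abstinence allows up to five cigarettes since the quit date and requires "salivary cotinine levels of less that 15 ng/ml". Neither definition mentions people who are still using NRT. The 28-day measure is checked differently, "with validation by carbon monoxide less than 10 ppm".

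*Trial medication* states: "Smokers in the current trial will all be prescribed NRT patches plus oral NRT" top-up. Full dose is intended for four weeks, "after which medication is reduced, according to patient need". No end date is stated.

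Hypothesis II concerns smokers who have failed to quit at six months. Its subgroup is defined twice. In the outcomes section: "The sub-group comprises those participants who fail to achieve prolonged abstinence at the six month follow-up". In the statistical analysis section the comparison is made among those not abstinent "as judged by 7-day point prevalence abstinence". The outcome is the mean of four 7-point items on intending, expecting, being determined and wanting to stop smoking in the next four weeks.

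**The concern.** Cotinine is a metabolite of nicotine and does not show whether the nicotine came from tobacco or from a patch, gum or lozenge. In a trial that gives NRT to everyone, a rule based only on cotinine can record a non-smoker as not abstinent. Carbon monoxide, used at 28 days when NRT is in full use, does not have this problem. The six-month rule has no comparable safeguard.

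Two results are at stake. Validated six-month abstinence would be understated, and the understatement would differ between arms if continuing NRT use did. The Hypothesis II comparison would also include people who do not smoke, for whom the motivation items have no clear meaning.

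**Working it through.** The plan gives no six-month quit rate and no rate of continuing NRT use, so there is no stated figure to reproduce. The check has two parts.

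**Tracing the rule.** Take a participant who has not smoked since the quit date and whose NRT keeps cotinine at 15 ng/ml or more.

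1. Point prevalence: the cigarette condition is met, the cotinine condition fails. Not abstinent.
2. Prolonged abstinence: the cigarette condition is met, the cotinine condition fails. Not abstinent.
3. Hypothesis II subgroup: the participant enters under the outcomes definition (by 2) and under the analysis definition (by 1).

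The two subgroup definitions are not the same. Anyone who meets the prolonged criterion also meets the point-prevalence criterion, because at most five cigarettes since the quit date implies at most five in the last week and the cotinine limit is shared. The analysis subgroup therefore lies inside the outcomes subgroup. The outcomes subgroup also holds people who smoked more than five cigarettes after the quit date but pass the point-prevalence test at six months.

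**Illustrating the size.** Let A be true six-month abstinence and s the share of abstainers on NRT with cotinine at or above 15 ng/ml. Both are assumptions: A = 15-20%, s = 5-20%. N = 630 comes from the plan, with complete follow-up assumed.

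- People misclassified = 630 × A × s
- Observed abstinence = A × (1 − s)
- Share of the Hypothesis II subgroup = A × s / (1 − A × (1 − s))

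| A | s | Misclassified | Observed abstinence | Share of subgroup |
|---|---|---|---|---|
| 15% | 5% | 4.7 | 14.25% | 0.0075/0.8575 = 0.9% |
| 15% | 20% | 18.9 | 12.0% | 0.03/0.88 = 3.4% |
| 20% | 5% | 6.3 | 19.0% | 0.01/0.81 = 1.2% |
| 20% | 20% | 25.2 | 16.0% | 0.04/0.84 = 4.8% |

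The range is about 5 to 25 people. Wider assumptions (A = 10-30%, s = 5-30%) give about 3 to 57 people and 0.6% to 11.4% of the subgroup, which shows how little the size is pinned down.

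**Difference between arms.** With equal true abstinence, the spurious difference is A × (difference in s between arms). If one arm had s = 10% and the other 5% at A = 15%, it is 0.15 × 0.05 = 0.75 points. With 20% and 10% at A = 20%, it is 0.20 × 0.10 = 2.0 points. The largest value within the assumed ranges is 0.20 × 0.15 = 3.0 points. The sign depends on which arm has more continuing users.

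For scale, the standard error of a difference in proportions with 315 per arm is √(2 × 0.15 × 0.85/315) = 2.8 points at 15% and √(2 × 0.20 × 0.80/315) = 3.2 points at 20%. The 95% interval is thus about ±6 points.

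**The case against.** The strongest reply is that this is a condensed article. It cites a published outcome standard alongside the cotinine limit, and that standard or the full protocol may say how declared NRT users are handled. The six-month questionnaire may already ask about NRT. This stands as a limit: the point concerns only what the article states. It does not remove the point, because the article writes out a complete operational rule, and that rule, applied as written, gives the wrong answer for these people.

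A reader might infer that every non-smoker still on NRT fails the test. That is too broad: only those at or above 15 ng/ml fail, and light or occasional users may pass. The planned dose reduction after four weeks also suggests that the number could be small.

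A reader might also infer that the error works against the genotype arm, because genotype tailoring is expected to raise NRT use. The documents do not support this. Hypothesis I is tested over 28 days, and the article expects the effect may be stronger in the first week. Nothing predicts longer use at six months in one arm. The interim look found more phenotype than genotype participants on the higher oral dose (32 v 14 of the first 160), which could push the other way. The cut-off was then changed to restore balance.

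Two further replies stand in part. The article does not say whether self-reported non-smokers answer the motivation items; without scores they would not enter the *t*-test. And under the outcomes definition, former lapsers who no longer smoke enter the subgroup whatever their cotinine, so cotinine is not the only route by which non-smokers get in.

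**Conclusion.** The point holds for the rule as the article states it. An abstinent NRT user with cotinine of 15 ng/ml or more is counted as not abstinent on both six-month measures and enters the Hypothesis II subgroup under either definition. About 5 to 25 of 630 people would be affected if true abstinence is 15-20% and 5-20% of abstainers are such users. Neither figure comes from the documents, so the actual number is unknown.

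A difference by arm is possible, but neither its direction nor its size is established. On the assumed ranges it would be at most about one standard error of the abstinence comparison. Six-month abstinence is a secondary outcome, and the article says the trial is not powered for long-term smoking behaviour. The 28-day adherence outcome does not use cotinine and is not affected. The change is worth making because it is cheap, and because cotinine alone cannot identify these people afterwards.

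**What to change.** 1. Make sure that current NRT use is recorded in the six-month questionnaire.
2. Keep the stated cotinine definitions for the main analysis.
3. Pre-specify a sensitivity analysis that counts as abstinent the self-reported abstainers who declare current NRT use and have cotinine of 15 ng/ml or more. Report their number by arm.
4. Repeat the Hypothesis II comparison without these people.
5. Reconcile the subgroup definitions in the outcomes section (prolonged abstinence) and the analysis section (7-day point prevalence), and use one throughout.

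The cost is at most one questionnaire item, one extra abstinence analysis and one repeat of the motivation comparison; no new biochemical test is needed. The drawback is that abstinence in this small group rests on self-report from participants who know their allocation, even though the article conceals allocation from the team collecting self-reported smoking status. That is why it should be a sensitivity analysis and not replace the main definition.

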#### Hypothesis II

##### i) Within-subgroup outcome: Motivation to make another quit attempt

The sub-group comprises those participants who fail to achieve prolonged abstinence at the six month follow-up. The primary outcome within this subgroup is motivation to stop smoking in the next four weeks.

This is measured using the mean score of the following four items measured using 7-point bipolar scales: "Do you intend to stop smoking in the next 4 weeks?"[response scale labelled at each end: "definitely do not" (1) and "definitely do" (7)]: "How likely is it that you will stop smoking in the next 4 weeks?" ["very unlikely" (1), and "very likely" (7)]; "How determined are you to stop smoking in the next 4 weeks?" ["not at all" (1), and "extremely" (7)]; and "How much do you want to stop smoking in the next 4 weeks?" ["not at all" (1), to "very much" (7)].

### Sample size calculation

With 315 participants per arm, there is 90% power to detect a 7.5% difference in the mean proportion of NRT consumed using a two-tailed test at the 5% level of significance. This is equivalent to detecting approximately a two days' worth difference in mean NRT consumption over a 28-day period. The calculation is based on the skewed distribution of days of prescribed NRT patch use reported by Alterman and colleagues [41] where 55% of participants reported high use and the remainder had a uniformly spread distribution of use. Assuming the same mixed distribution, with 50% and 65% of high-use participants and the remainder uniformly distributed in the two arms, the implied difference in mean consumption was 7.5%. By repeated random sampling, the distribution of the mean within each group was close to normal. The estimated pooled within-group standard error was 1.85%, and both Mann-Whitney and unpaired t-tests provided at least 90% power.

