### Outcomes

#### Hypothesis I

##### i) Primary outcome

The primary outcome is adherence to a 28-day prescription expressed as the proportion of all NRT prescribed (in milligrams) that is consumed each day in the first four weeks of quitting, averaged over the four week quit period.

The proportion consumed will be measured by self-report daily diary, backed up by pill counts. If pill counts are discrepant with the diary, this will be discussed and reconciled by the research nurse at the weekly clinic visit. The adherence proportion on any day is the ratio of the amount of NRT consumed to the amount prescribed. The denominator of the amount prescribed derives from both NRT patch and top up. For example, for someone prescribed 1 × 21 mg patch and 6 × 1 mg oral NRT doses (equivalent to 6 × 2 mg gums, for example), the denominator is 27 mg. Consumption of the prescribed top ups and any additional top ups taken will count towards the total NRT consumed on a day. Wearing the patch for 24 hours a day will count as the maximum amount of NRT mg prescribed as having been consumed from the patch. If the patch is worn for a fraction of the 24 hours (such as 12 hours) then this fraction of the total NRT mg from the patch will be counted as having been consumed (such as 0.5 × 21 mg for a 21 mg patch worn for 12 hours), pro-rata. If the patch is not worn for 24 hours a day but additional oral NRT is taken then this will count towards the total NRT consumed on that day. For example, if someone prescribed a 21 mg patch and 6 mg of oral NRT, wears their patch for 16 hours a day and uses an additional 7 pieces of gum to make up for the 7 mg of NRT lost by the patch coming off early, this will be treated as 100% adherence (i.e. they have consumed 14 + 6 +7 = 27 mg). NRT consumed above that prescribed on any day could occur through excess top up consumption and will be treated as a daily proportion of 100%. The daily proportion will be treated as 0% when no NRT is consumed, if, for example, a person has resumed smoking.

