#### Method

Each participant will be randomised to one of the two arms on a 1:1 basis. The randomisation will be stratified by nurse, cigarettes smoked per day (i.e., 10-14 or 15+) and the Fagerström Test for Nicotine Dependence score (< 7 (< 8) or 7-10 (8-10)). Within each stratum, a randomisation sequence will be generated using blocking, with successive randomly selected blocks sizes of six, eight and ten, in order to minimise predictability of assignment. Families will be allocated as clusters to the same arm to avoid contamination and reflect practice. First participants from families will be assigned a group according to the next blocked allocation in their stratum.

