### Statistical Analysis

All analyses will be primarily on an intention-to treat-basis, with the intention to treat population defined as those randomised into the trial. This compares the pragmatic policies represented by the two intervention arms amongst all those eligible and consenting. This will be supported by an explanatory per protocol analysis, with the per protocol population defined as all participants with the exclusion of those who chose not to attend to receive their allocated intervention.

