#### Handling missing data in the primary outcome

Analysis of adherence over the 28-day period will be primarily on an intention to treat basis, involving all randomised participants. If clinic non-attenders report returning to smoking or cannot be contacted by the nurse to establish adherence, then adherence will be counted as zero for the remaining 28 day period. Missing daily adherence data from those participants who attended the clinic session will be imputed from the average taken from the days that are not missing. This analysis will be supported first by an explanatory per protocol analysis which excludes those participants not receiving the intervention, and second, by a sensitivity analysis.

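### The stated 90% power for the primary t-test does not follow from the plan's own printed inputs (about 82–86%), and the model makes no explicit allowance for randomised people who never attend to receive their prescription

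*Protocol article*

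**What the plan says.** The Sample size calculation section states: "With 315 participants per arm, there is 90% power to detect a 7.5% difference in the mean proportion of NRT consumed". The significance test is two-sided at 5%. On the model it says: "The calculation is based on the skewed distribution of days of prescribed NRT patch use". The assumed arms have 50% and 65% high users, with the remainder uniform. From this the section derives a 7.5-point difference and a pooled within-group standard error of 1.85%, and claims at least 90% power for both the Mann-Whitney and the unpaired t-test. It has no term for people who never start.

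The outcome to be analysed is defined elsewhere. Under Primary outcome, adherence is daily milligrams consumed over milligrams prescribed, capped at 100% and averaged over four weeks: "The denominator of the amount prescribed derives from both NRT patch and top up". The Statistical Analysis section takes all participants, "with the intention to treat population defined as those randomised into the trial", and defines a supporting per-protocol set by "the exclusion of those who chose not to attend to receive their allocated intervention". Under Handling missing data in the primary outcome, if a clinic non-attender is smoking again or cannot be reached, "then adherence will be counted as zero for the remaining 28 day period". The Analysis of primary outcome section makes the independent-samples t-test the primary comparison, with a bootstrap interval as confirmation.

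On timing, the Consent process and Randomisation sections place allocation after a confirmatory telephone call. The Data collection section places the NRT prescription at the second clinic visit.

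**The concern.** Two questions arise. The first is whether the printed inputs yield 90% power for the t-test, which is the primary test. The second is whether the model describes the outcome as it will be analysed. People are randomised before they are prescribed anything, and the per-protocol definition shows that the plan foresees some who never come to receive their allocated intervention. They stay in the primary analysis, where no trial NRT means zero on every day. A cluster at 0% opposite a cluster at 100% widens the SD. It may also shrink the contrast, because the intervention is a message delivered with the prescription.

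At stake is how a null result is read. If 90% power is quoted for 7.5 points, a non-significant t-test will be taken as stronger evidence against an effect of that size than the design supports.

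**Working it through.** **Inputs from the protocol article.** n = 315 per arm; 1:1 allocation ("Each participant will be randomised to one of the two arms on a 1:1 basis"); two-sided 5%; high-use shares p = 0.50 and 0.65; difference 7.5 points; within-group standard error 1.85%.

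**Assumption on high use.** The stated difference fixes the gap between high users and the rest: 0.15 × gap = 7.5 points, so gap = 50 points. The simplest reading is high use = 100% and the rest uniform on 0–100% (mean 50%).

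**Step 1: the plan's mixture, no extra zeros.** With a share q of full-period zeros, the mean is (1−q)(1+p)/2, E[X²] is (1−q)(1+2p)/3, and the variance is E[X²] − mean². At q = 0:
- p = 0.50: mean 0.750, variance 0.6667 − 0.5625 = 0.1042, SD 32.3%.
- p = 0.65: mean 0.825, variance 0.7667 − 0.6806 = 0.0860, SD 29.3%.
- Difference 7.5 points (reproduced). Pooled SD = √0.0951 = 30.8%. SE = 30.8/√315 = 1.74% (the plan prints 1.85%).

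Power = Φ(difference / (SD × √(2/315)) − 1.96). The SE of the difference is 30.84 × 0.0797 = 2.457, so power = Φ(7.5/2.457 − 1.96) = Φ(1.09) = **86%**. Simulation of the t-test (4,000 trials) gives about 85%. Mann-Whitney gives about 95%, so the 90% claim reproduces for that test only.

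**Step 2: the printed standard error.** SD = 1.85 × √315 = 32.8%. The SE of the difference is 1.85 × √2 = 2.616, so power = Φ(7.5/2.616 − 1.96) = Φ(0.91) = **82%**. This needs no assumption about the shape of the distribution. At n = 315, 90% power needs an SD of at most 29.0%. Reading 1.85% as the SE of the difference would give 98%, but the text calls it within-group, and it would imply an SD of 1.85/0.0797 = 23.2%, well below the mixture's.

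**Step 3: adding full-period zeros.** The documents give no rate, so q is assumed, equal in both arms. At q = 5% the variances are 0.6333 − 0.7125² = 0.1257 and 0.7283 − 0.78375² = 0.1141, so the pooled SD is 34.6%. The diluted difference is 7.5 × (1−q). The difference detectable with 90% power is 3.2415 × SD × √(2/315).

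| q (assumed) | SD | Power, 7.5 points held | Power, diluted | Detectable with 90% power |
|---|---|---|---|---|
| 0% | 30.8% | 86% | 86% | 8.0 points |
| 2% | 32.5% | 83% | 81% | 8.4 points |
| 5% | 34.6% | 78% | 73% | 8.9 points |
| 10% | 37.6% | 71% | 61% | 9.7 points |

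The printed SD of 32.8% corresponds to q of about 2.5%; with that SD the detectable difference is 8.5 points. If 10% zeros replace only members of the uniform remainder, the difference stays at 7.5 points, the SD is about 37.2% and power about 72%.

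**The case against.** Several objections carry weight.

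- **The source distribution may already contain never-users.** A reader might infer that the SD is understated by a known amount, or that the 90% really describes patch days among treatment starters only. The documents support neither. The sample size section speaks of participants and does not say who was counted. The printed SE already exceeds the mixture's by about what 2.5% zeros would add.
- **No rate is given.** The call confirming commitment before randomisation should limit non-attendance. The 2–10% range is illustrative.
- **Dilution is a further assumption.** The 50%/65% contrast may be meant for everyone randomised. The held-difference column is then the relevant one.
- **Part-way dropouts are not a new cluster.** The missing-data rule zeroes only the days that remain, so these people fall in the uniform part, which already reaches towards zero. Only never-starters add a separate mass.
- **Milligrams versus days could move the SD either way**, since top-up can offset lost patch time and each day is capped at 100%. Planning on a related measure is ordinary practice.
- **High use need not mean 100%.** If high use were uniform on 80–100% (mean 90%) and the rest uniform on 0–80% (mean 40%), the gap is still 50 points. The variances are then 0.5133 − 0.65² = 0.0908 and 0.6033 − 0.725² = 0.0777, the pooled SD is 29.0% and power about 90%. But the SE would then be 29.0/√315 = 1.64%, further from the printed 1.85%. This reading cannot be combined with the printed SE.
- **A confidence interval is planned**, so a null result need not be judged on planned power alone.

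These points remove any claim to a known loss from non-attendance. None of them reconciles an SE of 1.85% with 90% t-test power.

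**Conclusion.** The concern holds in a limited form. The 90% claim for the primary t-test is inconsistent with the plan's own printed figures: about 82% from the stated SE, whatever the shape of the distribution, and about 86% from the stated mixture if high use means full use. The claim is met for Mann-Whitney, which is not the primary test.

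Beyond that, the model has no explicit place for randomised people who never attend for their prescription, although the plan foresees them and would score them zero throughout. The further loss is a sensitivity range resting on an assumed rate, equal in both arms. It is not an established understatement of the SD. No change in sample size follows; what needs correcting is a stated number and the assumption behind it.

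**What to change.** In the Sample size calculation section, keep 630 participants and:

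1. Restate the t-test power as about 82–86% from the plan's own inputs, say what level of use counts as high, and reconcile the printed SE with the mixture. Attribute the figure of at least 90% to Mann-Whitney only.
2. Rerun the simulation with a stated full-period-zero fraction: an assumed range such as 2–10%, or a pooled, arm-blind rate if the trial holds one. The interim look at the first 160 participants is reported only for dose counts, so such a rate cannot be presumed to exist. Say whether the source distribution already includes never-users.
3. Report the resulting t-test power, with the difference held and diluted, and the difference detectable with 90% power.

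The cost is one rerun of an existing simulation and a reworded paragraph. It needs no extra participants or data and no change to the analysis. The stated power becomes less favourable.

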#### Hypothesis I: Analysis of primary outcome

For the analysis of the primary outcome, the proportion of all NRT consumed in the first 28 days of quitting will be compared between arms using an independent samples t-test and by estimating the 95% confidence interval for the observed between-arm difference in mean of proportion of NRT consumed (Hypothesis I). This will be confirmed using the nonparametric Bootstrap BCA method for estimating the difference between two means with confidence interval.

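### The printed within-group standard error of 1.85% implies about 82% power for the primary t-test, not the stated 90%

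*Protocol article*

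**What the plan says.** The protocol article, under Sample size calculation, states: "With 315 participants per arm, there is 90% power to detect a 7.5% difference in the mean proportion of NRT consumed". The significance level is 5%, two-sided. The planning distribution is a mixture. Half of one arm and 65% of the other are high users, and everyone else is spread uniformly. From this, "the implied difference in mean consumption was 7.5" per cent. The section adds that, in repeated sampling, the group means were close to normally distributed, and closes: "The estimated pooled within-group standard error was 1.85%, and both Mann-Whitney and unpaired t-tests provided at least 90% power".

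Under Hypothesis I: Analysis of primary outcome, the proportion of NRT consumed "will be compared between arms using an independent samples t-test", with a 95% confidence interval and a bootstrap check of the same difference in means. The Mann-Whitney test is not part of the primary analysis.

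**The concern.** The section prints the sample size, the difference, the significance level, the standard error and the power. The first four fix the fifth, and the printed power is not the one they give.

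The claim of at least 90% is made for both tests, but only the t-test carries the primary conclusion. If the printed standard error is right, the chance of missing a true 7.5-point difference is about 18%, not 10%. A reader of a null result would then credit the trial with more ability to exclude that effect than it had. The Abstract also tells readers that 630 smokers give sufficient power for 7.5%.

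**Working it through.** **Inputs** (all from Sample size calculation, except the choice of test, which is from the analysis of the primary outcome): n = 315 per arm; difference 7.5 percentage points; two-sided 5%, so z = 1.960; within-group standard error 1.85%; unpaired t-test. For 90% power, z = 1.282.

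**1. The difference reproduces.** Take high use as 100% and the remainder as uniform on 0-100%. The arm mean is then p + (1 − p)/2, which is 0.750 for p = 0.50 and 0.825 for p = 0.65. The difference is 7.5 points, as printed.

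**2. Power from the printed standard error.**
- Implied SD: 1.85% × √315 = 32.8%.
- SE of the difference: 1.85 × √2 = 2.62 points.
- Standardised difference: 7.5 / 2.62 = 2.87.
- Power: Φ(2.87 − 1.96) = 81.8%; the noncentral t gives 81.7%.
- Rounding of 1.85% (1.845 to 1.855) moves this only between 82.0% and 81.6%.
- Difference detectable with 90% power: (1.960 + 1.282) × 2.62 = 8.5 points.
- Within-group SE needed for 90% at 7.5 points: 7.5 / (3.242 × √2) = 1.64%.

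Because the section itself reports near-normal means, this step does not depend on the shape of the raw distribution.

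**3. Other readings of 1.85%.** If it were the SE of the difference, 7.5 / 1.85 = 4.05 and power would be Φ(4.05 − 1.96) = 98%. A one-sided 5% test with 1.85% per arm gives 88.9%. The text says within-group and two-tailed, and neither alternative gives 90%.

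**4. What the verbal mixture implies.** High use is not defined, so two readings were compared.

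*High use = 100%, remainder uniform on 0-100%.* The variance is p + (1 − p)/3 − mean², so the SDs are 0.323 and 0.293 and the pooled SD is 0.308. The SE is 0.308/√315 = 1.74%, and the SE of the difference is 2.46 points. Power is Φ(7.5/2.46 − 1.96) = 86% (simulated 85.8%). Simulated Mann-Whitney power is about 95%.

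*High use = uniform on 80-100%, remainder uniform on 0-80%.* The component means are 0.90 and 0.40, so the difference is 0.15 × 0.50 = 7.5 points again. The component variances are 0.20²/12 = 0.0033 and 0.80²/12 = 0.0533. The arm variance is 0.0033p + 0.0533(1 − p) + 0.25p(1 − p), which is 0.0908 and 0.0777. The pooled SD is 0.290, the SE 1.64% and the t-test power 90%. Simulated Mann-Whitney power is about 91%.

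Any cut-point c between a high band (c to 100%) and a remainder (0 to c) gives component means exactly 0.50 apart, and so a 7.5-point difference. Matching 7.5 points therefore does not identify the reading that was used. Neither reading above gives an SE of 1.85%.

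**The case against.** The strongest reply is that the power may be right and the standard error wrong. The wording of the mixture is compatible with 90% for the t-test if high use was a band such as 80-100%. The figure of 1.85% could also come from another sample size. On the 100% reading it would match about 278 per arm, since (0.308/0.0185)² ≈ 278, although the document does not say so. This reply stands as far as it goes: the text shows an inconsistency, not which number is faulty. It does not remove the contradiction, because every route to 90% requires the printed 1.85% to be wrong.

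It also limits what may be concluded. A reader might infer that true t-test power lies between 82% and 86% and that the 90% belongs to the Mann-Whitney test alone. The 86% rests on equating high use with 100%, which the document does not do, and the band reading gives 90% for the t-test as well.

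A reader might also infer that power is lower still, because under Handling missing data in the primary outcome, for non-attenders who report smoking again or cannot be contacted, "then adherence will be counted as zero for the remaining 28 day period". This is not shown. The rule sets only the remaining days to zero, so someone lost part-way keeps an intermediate average, which a uniform remainder can already represent. Exact zeros arise only for people who use no NRT at all. The document gives no proportion for them.

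Finally, the primary result will be reported with a confidence interval, which shows directly what a null result excludes. That softens the consequence but leaves the planning statement incorrect.

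**Conclusion.** The point holds for the printed figures. A within-group standard error of 1.85% and at least 90% t-test power for 7.5 points cannot both be right with 315 per arm and a two-sided 5% test. If the standard error is correct, power is about 82%, and the difference detectable with 90% power is about 8.5 points. If the power is correct, the standard error should be no more than 1.64%. The first result needs only the printed inputs and approximately normal means. The document does not settle which figure is in error, because the range that counts as high use and the range of the remainder are not given. The Mann-Whitney claim is not in dispute: it exceeded 90% under every mixture tried.

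**What to change.** Keep the sample size at 630. State the range that counts as high use and the range over which the remainder is uniform. Rerun the planning calculation for the independent-samples t-test, and report its power and the matching within-group standard error. Then correct whichever printed figure is wrong. If 1.85% stands, restate power as about 82% for 7.5 points or, equivalently, 90% for about 8.5 points, and bring the Abstract's statement of sufficient power into line.

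Optionally, add a sensitivity run in which an assumed share of randomised participants use no NRT and score zero, with that share labelled as an assumption.

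The cost is a text correction and one rerun of the planning simulation. The outcome, the test and recruitment do not change. The stated power may become less favourable.
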